### Sample size

This study is designed as a superiority trial. A previous findings showed the ACR20 response rates were 34.3% in a topical TwHF group and 12.5% in placebo group in patients with active RA [awaiting publication]. Based on the following calculation: *n* = 2(u_α_ + u_β)_
^2^2P(1-P)/(P_1_-P_0_)^2^ [13], it is predicted that 76 participants in each group will be needed to detect a significant (p < =0.05) with 80% power. Based upon a predicted 10% rate of drop out, we will recruit a total of 168 participants, 84 in each group.

### Quality control

The identification, registration, and subsequent flow of participants in the trial will be governed by the trial standard operational protocol. The completion of the Case Report Form and compliance with the standard operation procedures will be audited. At regular intervals, a clinical research associate, will monitor the clinical trial procedures, such as compliance with the study protocol and regulatory policy. In particular, the reasons for withdrawal will be fully documented in the Case Report Form.

### Data analysis

The statistical analyses will be performed using the intention to treat analysis (ITT). The safety dataset will also include all patients who received ≥1 week of topical applications. Mean ± Standard Deviation, number and percentage will be used for continuous variables and categorical variables, as appropriate. Patient movement through the study will be documented on a Consort diagram. Patient demographic characteristics will be documented in a by-group comparison table and statistically compared between topical TwHF and placebo groups using a 2-sample t test for continuous variables or Pearson 2 test for categorical variables.

All analyses will be performed using SAS system (Version 5.2.127 8.2 for Windows). *P* values less than .05 will be considered statistically significant. The primary outcome variable, the ACR20 response rate at week 8, and the secondary outcome measure, ACR20 at week 4 and ACR 50 response rate at weeks 4 and 8, will be compared between the 2 groups using the Pearson 2 test. Two-sample t tests will be performed on DAS28-CRP and DAS28-ESR at baseline and posttreatment, as well as their changes after treatment. Paired t tests will be used to compare the changes of DAS28-CRP and DAS28-ESR from baseline to posttreatment in each group. The joint synovitis classification will be compared between the 2 groups at baseline and posttreatment using Kruskal-Wallis rank sum test. Any by-group changes in the joint synovitis classification will be compared using the paired Kruskal-Wallis rank sum test.

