**Methods:**

This study will be an 8-week double-blinded, randomized, placebo-controlled clinical trial conducted at Guang’anmen Hospital in Beijing, China, and 168 patients with moderately active RA will be randomly assigned with a 1:1 ratio to apply a topical gel preparation containing TwHF or placebo. The primary outcome variable will be the proportion of subjects, by study group, to achieve a 20% improvement in the American College of Rheumatology criteria (ACR20) by week 8. Secondary outcome measures to be assessed at weeks 4 or 8 will include: measurement of ACR20 response rate at week 4, ACR50 response rate, the changes in DAS28 score, and joint synovitis classification assessment monitored by musculoskeletal ultrasound. Safety evaluations conducted at weeks 4, 8 and 12 will be based on spontaneous complaints by the study subjects, but special emphasis will be focused on cutaneous allergy and alterations of menstruation in premenopausal female participants. Statistical analyses will be performed using the intention to treat analysis data set.

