### Intervention

The ingredients for the compounding of the topical TwHF gel include: Tripterygium wilfordii Hook F, Mangxiao (Mirabilite), Chuanxiong (Rhizoma Ligustici), Ruling (Olibanum), and Moyao (M yrrh) (proportions: 4:4:2:2:1). The topical placebo gel is made of a viscous agent and sucrose which make it looks like the active preparation. Both of the gels will be prepared by the Pharmaceutical Department of Guang’anmen Hospital, and the herbs will be purchased from Beijing Fengtaijinyuan Pharmaceutical Co., Ltd. Each gel is 20 gram (g) per tube. Both the topical compound TwHF gel and the placebo gel will be applied for 1st to 5th metacarpophalangeal joints, 1st to 5th proximal interphalangeal joints, wrists, knees and ankles 10 g for 1 h, once a day from week 0 through week 4 and 10 g from week 5 through week 8.

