The safety evaluation will be accomplished by a face-to-face interview at the 4th and 8th weeks and by a a telephone-interview with the remote 12th week follow-up. Adverse experiences of interest will include: manifestations of cutaneous allergy (erythema, edema, itching) and gastrointestinal stimulation due to mucous membrane damage. In addition, because of the high frequency of reproductive system damage, the safety evaluation will focus on changes in menstruation patterns among premenopausal female participants. The relevant female participants will be asked a general question about whether they have observed any change in their menstruation pattern. Irrespective of how they answer that question, a series of follow-up questions will attempt to quantify any change in the menstrual cycle (extension, shortening or no change), or in the quantity of menstrual flow (increased, reduced, or unchanged). Blood and urine routine laboratory examinations, including glutamic-pyruvic transaminase, glutamic oxalacetic transaminase, creatinine and urea nitrogen will be accomplished at baseline and on the 8th week. Quantitative changes will be addressed on the record. Professional judgments regarding the severity of any given adverse effect and any recognized relationship between the adverse effect and the study interventions will be documented if any of the above safety measures are observed to fall beyond normal clinical or laboratory ranges.

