## Discussion

To date, only a small number of studies have documented the effectiveness of CET using any pharmacological agent. This clinical trial is designed as a double-blinded, randomized, controlled study of TwHF-based CET in a moderate active RA population with 8 weeks of observation. Considering the main clinical features of active RA to be joint swelling, tenderness, and pain, these are the clinical manifestations monitored using validated instruments. It is anticipated that topical compound TwHF gel will also be effective in controlling the clinical manifestations of RA and safe for use by RA patients.

In animal studies, TwHF microemulsion has been observed to imeliorate the severity of a murine adjuvant-induced arthritis model and to reduce the male reproductive toxicity and hepatotoxicity [14]. It is hoped that the topical use of TwHF as a clinical application of CET in RA patients will be found to be both safe and efficacious. Although TwHF and its extracts have shown good responses in patients with RA it is currently limited to use in elderly patients because of demonstrated reproductive toxicity. Safety observations from previous studies have shown that compound TwHF applied topically can cause cutaneous reactions which are reversible with discontinuation of the topical TwHF compound. In addition, increases in serum aminotransferase and alterations in menstruation among female patients have been reported [5, 6].

There are several aspects of the current study design that are different from previous CET clinical studies using this agent. Firstly, the design of dosage adjustment in this study will demonstrate whether the period of dosage reduction will bring additional benefits to the patients. In clinical practice, patients often continue to apply the effective medicine for an additional period in order to consolidate the efficacy, though there is no evidence to support this practice. Secondly, the follow-up assessment has rarely been included in CET research. Since oral preparations of THwF have often exhibited side effects, such as gastrointestinal and menstrual disorders, special emphasis has been placed upon an 4-week follow-up (to monitor at least one menstrual cycle).

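### The safety set is defined by at least one week of gel use, so early stoppers with a skin reaction can fall out of the adverse-event rates

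*Protocol article*

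**What the plan says.** The Data analysis section first commits the statistical analyses to intention to treat, then adds a separate rule for safety: "The safety dataset will also include all patients who received ≥1 week of topical applications". No other section defines the safety set, and none says that patients with shorter exposure are kept in it.

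Three other places bear on the rule:

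- **Abstract, Methods.** For safety, "special emphasis will be focused on cutaneous allergy and alterations of menstruation in premenopausal female participants".
- **Outcome measurements.** The adverse experiences of interest include "manifestations of cutaneous allergy (erythema, edema, itching) and gastrointestinal stimulation due to mucous membrane damage", and the safety evaluation is also to focus on menstrual change. On timing: "The safety evaluation will be accomplished by a face-to-face interview at the 4th and 8th weeks", with a telephone interview at week 12.
- **Discussion.** Previous studies are said to show that "compound TwHF applied topically can cause cutaneous reactions which are reversible with discontinuation of the topical TwHF compound".

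The Intervention section has the gel applied "once a day from week 0 through week 4", so one week of use means about seven applications.

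**The concern.** A safety set should hold everyone exposed to the product. Here, entry depends on something that happens after randomisation, namely continuing with the gel for a week, and a reaction to the gel can itself prevent that. A patient who develops erythema or itching on day 2 and stops has about two applications and does not qualify. The person with the event and the event itself both disappear from the safety table.

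The affected harm is one the trial says it will emphasise, and the article itself reports that the topical compound can cause it. The placebo is a viscous agent with sucrose, and the article reports no skin reactions for it. Early losses of this kind would therefore plausibly be more frequent on TwHF, which would pull the between-arm comparison towards no difference in harm. Safety is one of the stated aims of the trial, and the conclusion looks ahead to a claim that the gel is safe.

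**Working it through.** The plan states no figure for this point, so there is nothing to reproduce. The check has a reading part and an illustrative part.

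**Reading the rule.** There are two candidate readings.

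1. Minimum exposure: the safety set consists of patients with at least one week of applications. Early stoppers are out.
2. Addition: the safety set is the ITT set, and patients with at least one week of applications are added to it. But those patients were randomised and are already in the ITT set, so the condition would do nothing.

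Only the first reading gives the one-week condition any effect, so it is the natural one.

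**Inputs.** 84 patients per arm (Sample size). Two quantities are assumed, because the article gives no rate or timing of early skin reactions: *k* = patients in an arm who react and stop before one week; *m* = other patients in that arm who react. All 84 are taken to have had at least one application, and nobody else is taken to stop in week 1.

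**Formulas.**

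- Rate in all treated patients: (k + m)/84
- Rate in the one-week set: m/(84 − k)

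The second is below the first whenever k > 0 and k + m < 84: cross-multiplying, 84m < (k + m)(84 − k) reduces to k(k + m) < 84k. Under these assumptions the direction does not depend on the values chosen; the size does.

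| k | m | All treated | One-week set |
|---|---|---|---|
| 1 | 4 | 5/84 = 6.0% | 4/83 = 4.8% |
| 4 | 4 | 8/84 = 9.5% | 4/80 = 5.0% |
| 4 | 8 | 12/84 = 14.3% | 8/80 = 10.0% |
| 8 | 8 | 16/84 = 19.0% | 8/76 = 10.5% |

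If the placebo arm has no early stoppers, its rate is unchanged and the whole fall in the TwHF rate passes into the difference between arms. With k = m = 4 that is 9.5 − 5.0 = 4.5 percentage points.

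**How likely is any exclusion?** If a proportion *r* of an arm stops in week 1, the expected number excluded is 84r, and the chance of excluding at least one patient is 1 − (1 − r)^84.

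| r (assumed) | Expected number excluded | Chance of at least one |
|---|---|---|
| 1% | 0.8 | 57% |
| 2% | 1.7 | 82% |
| 5% | 4.2 | 99% |

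**The case against.** **The wording is not exclusive.** The sentence says the set will *also include* these patients; it does not say *only*, and it never states that shorter exposures are left out. This stands as a real ambiguity. It does not rescue the rule, because the inclusive reading makes the threshold redundant, and a sentence open to both readings needs rewriting anyway.

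**Early stoppers remain visible.** The Quality control section requires reasons for withdrawal to be recorded in full in the Case Report Form, and the Data analysis section promises a CONSORT diagram. This also stands in part. A reader might infer that withdrawals for intolerance would be hidden or under-reported; the documents do not support that, since they can be traced among all randomised patients. Neither record puts these patients into the adverse-event rates, however.

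**Skin reaction is not shown to be the main harm.** A reader might infer that it is. The abstract names it alongside menstrual change, Outcome measurements also lists gastrointestinal effects and focuses on menstruation because of reproductive toxicity, and the Discussion adds raised aminotransferases. Skin reaction is one emphasised harm among several.

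**Reactions are not shown to make patients stop.** A reader might infer this from the Discussion. It says only that reactions resolve once the gel is stopped. It does not say how often patients stop or when. The exclusion criteria also keep out patients with skin allergy or broken skin at the treatment sites, which may lower the number of reactions. The point needs only that some reactors stop within a week.

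**Efficacy is untouched.** Correct: the ITT analyses, including ACR20 at week 8, do not use the safety set, and the section names no between-group safety test.

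**Conclusion.** The safety-set rule is wrong as written. On its natural reading it conditions the safety analysis on having continued the gel for a week and can understate the skin-reaction rate, plausibly more in the TwHF arm.

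The size cannot be derived from the article. Over the assumed values shown, the rate falls from 6.0% to 4.8% at the mild end and from 19.0% to 10.5% at the other. A reader might take the fall to about half (9.5% to 5.0%) as the expected effect; that case arises only because half of the reactors were assumed to stop in the first week. The greater loss on TwHF is likewise an inference from the article's account of skin reactions to the topical compound, not a figure it gives. If nobody stops in week 1, the rule has no effect. At an assumed early-stopping rate of only 2%, at least one patient in an arm would be excluded with 82% probability.

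**What to change.** Replace the sentence with a definition of the safety set as all randomised patients who received at least one application of study gel, analysed by the gel received, and delete the one-week minimum. Drop *also*, so that the set stands on its own and is not read as an extension of the ITT set.

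The cost is one sentence. It changes no treatment or visit, and the reasons for withdrawal needed to count early stoppers are already due to be recorded in the Case Report Form. The change should be made and dated before unblinding, because a later change to the safety denominator would look driven by the data.

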### Participants

#### Inclusion criteria

Eligible patients, men and women, must age from 18 to 65 years old, and must be clinically diagnosed with RA prior to screening for study entry in accordance with the 1987 revised criteria of the American College of Rheumatology [9]. Their RA disease stage must be in the moderate activity range, as defined by the criteria of the 28-joint count Disease Activity Score (DAS-28 score), ranging between 3.2 to 5.1 [10]. If patients are receiving a disease-modifying, anti-rheumatic drugs (DMARDs), those medications should be continued unchanged throughout this study, but their dosages must have been stable for at least 12 weeks prior to study entry.

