### Randomization

Randomization will be controlled by an independent third party, the hospital Clinical Evaluation Center, using the SAS system (Version 8.2 for Windows) to assign the eligible participants at a 1:1 ratio to receive either topical compound TwHF gel or placebo.

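### The primary ACR20 test is valid but leaves baseline DAS28 and DMARD use unused; a prespecified adjusted model would bring a small gain at almost no cost

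*Protocol article*

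**What the plan says.** All references are to the Protocol article.

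- **Data analysis.** ACR20 at week 8 is the primary outcome and "will be compared between the 2 groups using the Pearson 2 test" (the chi-square symbol was lost when the text was read). The threshold is that P "values less than .05 will be considered statistically significant". No adjusted or stratified analysis of ACR20 is described, either as primary or as support. Baseline characteristics are tabulated and tested between groups, but nothing follows from those tests.
- **Inclusion criteria.** Entry requires a "28-joint count Disease Activity Score (DAS-28 score), ranging between 3.2 to 5.1". Background treatment is conditional: "If patients are receiving a disease-modifying, anti-rheumatic drugs (DMARDs" is how the sentence opens, and it goes on to require stable, unchanged dosing. Patients may therefore enter with or without a DMARD, and both facts are on record before allocation.
- **Randomization and Blinding.** An independent centre uses SAS "to assign the eligible participants at a 1:1 ratio to receive either topical compound TwHF gel or placebo". No stratification or other balancing factor is named.

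**The concern.** Two baseline variables that could plausibly bear on response are collected for every patient, and the primary analysis ignores both. If they predict ACR20, an unadjusted comparison is somewhat less precise than it could be. The estimate also carries whatever chance imbalance in them arises in a single-centre trial of 168 patients.

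ACR20 is defined relative to baseline, but that does not make it independent of baseline. For the joint-count components, a patient with four tender joints meets the 20% threshold by losing one (25%), while a patient with twenty must lose four. Entry is set by a DAS28 range and not by a joint count. DMARD use is not a component of ACR20 at all.

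The planned significance tests of baseline characteristics do not help. If they show a difference, any adjustment made in response would be post hoc.

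**Working it through.** **Inputs.** ACR20 rates, from Sample size: "ACR20 response rates were 34.3% in a topical TwHF group and 12.5% in placebo group". Size, from the same section: "76 participants in each group will be needed to detect a significant (p < =0.05) with 80% power", raised to 84 per group for dropout. Alpha is 0.05; sidedness is not stated and two-sided is assumed. The article gives neither the prognostic strength of the covariates nor the share of patients on DMARDs, so both are assumptions. The simulation uses a 60% DMARD share, and the imbalance check uses 30% to 70%.

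**1. The plan's own figure.** The mean rate is P = (0.343 + 0.125)/2 = 0.234, and the difference is 0.218. The usual formula gives n = 2(1.96 + 0.8416)² × 0.234 × 0.766 / 0.218² = 2 × 7.849 × 0.1792 / 0.04752 = 59.2 per group. The formula as printed has a further factor of 2 and gives 118.4. Neither is 76.

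Power at 76 per group: (0.218 − 1.96 × √(2 × 0.1792/76)) / √((0.343 × 0.657 + 0.125 × 0.875)/76) = (0.218 − 0.1346)/0.0664 = 1.26, which is 89.6%. At 84 per group it is 92.3%. The mismatch is a separate matter. It is relevant here only because it places the starting power near 90%.

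**2. Power with and without adjustment.** There were 3,000 simulated trials per setting, with 76 per group and marginal rates held at 34.3% and 12.5%. DAS28 enters as a standardised normal covariate and DMARD use as a yes/no covariate. The Pearson test is compared with the likelihood-ratio test for treatment in a logistic model containing both.

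| Log odds ratio, DAS28 per SD / DMARD use | Odds ratio per SD | Power, Pearson | Power, adjusted | Type I error, Pearson / adjusted |
|---|---|---|---|---|
| 0 / 0 | 1.0 | 91.0% | 90.8% | 5.5% / 5.8% |
| 0.3 / 0.3 | 1.35 | 90.7% | 91.2% | 5.5% / 5.6% |
| 0.5 / 0.5 | 1.65 | 89.5% | 91.4% | 5.6% / 5.3% |
| 0.8 / 0.8 | 2.2 | 90.1% | 93.6% | 4.7% / 5.0% |
| 1.2 / 0.8 | 3.3 | 90.3% | 95.2% | 5.0% / 5.7% |

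The Monte Carlo standard error of a power figure is √(0.9 × 0.1/3000), about 0.5 point. The last row needs an odds ratio of 3.3 per SD, outside the range of 1.0 to 2.5 used for the conclusion. A second simulation at the same size used a single covariate with odds ratios of 1.3, 1.5, 2.0 and 2.5 per SD. The variance of the risk difference fell by 0.5%, 1%, 5% and 11%, and power changed by 0, 0, +1.5 and +2.1 points. With no prognostic effect, the variance rises by about 2%.

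Where power starts nearer 80% (58 per group), the two-covariate gain is a little larger: 81.9% to 84.4% at 0.5/0.5, and 80.9% to 85.7% at 0.8/0.8.

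**3. Chance imbalance at 84 per group.** For a standardised covariate, the SD of the difference in means is √(2/84) = 0.154, so an imbalance beyond 1.96 × 0.154 = 0.30 SD arises 5% of the time. The resulting shift in the ACR20 difference is about 0.30 × ln(OR) × 0.17, where 0.17 is the mean of p(1 − p) over the two groups.
- Odds ratio 1.5: 0.30 × 0.405 × 0.17 = 2.1 points.
- Odds ratio 2.0: 0.30 × 0.693 × 0.17 = 3.5 points.

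For DMARD use, the SD of the difference in proportions is √(2π(1 − π)/84), where π is the share on DMARDs: 7.1 points at 30% or 70%, and 7.7 points at 50%. A gap of 10 points or more therefore has a chance of about 16% to 19%.

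**4. Scale.** The standard error of the ACR20 difference at 84 per group is √(0.343 × 0.657/84 + 0.125 × 0.875/84) = 6.3 points. A shift of 2 to 4 points is below one standard error.

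**5. Model size.** Expected responders are 84 × (0.343 + 0.125) = 39, or about 13 per model term with three terms.

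**The case against.** The strongest objection is that nothing here is wrong. A Pearson test of two proportions is valid under randomisation, it agrees with the unadjusted two-proportion sample size, and its simulated type I error stays near 5%. That stands. A reader might infer that the primary test is biased or anti-conservative; neither the article nor the calculations support this.

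A reader might also infer that randomisation was unstratified and hence deficient. The article condenses the protocol and gives randomisation very briefly, so one can say only that no balancing factor is described.

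It would be tempting to say that adjustment removes the effect of chance imbalance. It does not. Chance imbalance is already part of the sampling error that the Pearson test allows for, and a model reduces its effect only for the covariates included and only as well as the model fits.

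The prognostic premise is assumed. No section says that DAS28 or DMARD use predicts ACR20. The entry range of 3.2 to 5.1 probably weakens DAS28 as a predictor, and the requirement for stable, unchanged DMARD doses limits DMARD-driven change during the trial. The joint-count example also points more directly to joint counts than to DAS28, and it covers only part of the ACR20 definition. These points stand and keep the expected gain small.

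What does not stand is that this is merely detail left to another document. The article names and fixes the primary test, and a better use of data already collected can be proposed against that stated choice.

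**Conclusion.** This is a minor efficiency improvement, held with low confidence as to its size. The plan's test is sound but sets aside two baseline variables it already has. Over assumed odds ratios of 1.0 to 2.5 per SD, with 76 per group and the plan's own rates, adjustment adds about 0 to 4 points of power to a starting value near 90%. The gain may be nil if the covariates are weakly prognostic, and there is then a negligible loss of precision (about 2% in variance). The protection against imbalance is real but partial. The conclusion rests on the assumed prognostic strengths and DMARD share, a two-sided 5% test, and the rates in Sample size.

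**What to change.** Replace the primary-analysis wording with one prespecified statement:

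- ACR20 at week 8 is analysed by logistic regression on treatment, baseline DAS28 (continuous) and background DMARD use at entry (yes/no), with treatment tested by the likelihood-ratio test.
- One DAS28 version is fixed in advance, for example DAS28-ESR, because Outcome measurements allows the CRP or the ESR version.
- The effect is reported as the standardised risk difference with its 95% CI.
- The Pearson test is kept as a supporting analysis.

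The covariates should be chosen now and not on the strength of the baseline significance tests. The cost is a sentence of text and a little more analysis work. No new data and no change in sample size are needed.
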